### Sample size

The sample size was informed by the faecal 16S rRNA gene amplicon datasets generated for the proof-of-concept study of 12 to 18-month-old Bangladeshi children with MAM.^11^ In that study, we identified 209 bacterial Amplicon Sequence Variants (ASVs) that were present above 5 counts in at least 5% of the 939 faecal samples analyzed from 118 participants. We calculated 95% confidence intervals (CI; mean ± 1.96 standard error) for the change (delta) in abundance of each of the 209 ASVs between day 0 (pre-intervention) and 4 weeks of intervention for the 59 children in the MDCF-2 treatment group of the POC study. Using a bootstrapping approach with ASV data from 5000 subsets of 20 children from the MDCF-2 group and 5000 subsets of 20 children from the RUSF group, we identified 121 ASVs whose mean changes in abundance for the MDCF-2 subsets fell within the 95% CI of the mean changes for the 59 MDCF-2 participants, but not in children who had received RUSF, with 80% power (“MDCF-2-responsive ASVs”). Therefore, each arm will include a minimum of 20 children who complete the study. Considering potential drop-outs (15%), 23 children will be recruited per arm.

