### Analysis plan

To assess the comparability of microbiota repair elicited by shelf-stable test formulations of MDCF-2 and the reference kitchen prepared formulation, we will sequence PCR amplicons generated from variable region 4 of bacterial 16S rRNA genes present in DNA isolated from faecal samples collected from participants in the different study arms immediately prior to intervention (day 0) and at the end of intervention (day 28). ASV data will be processed using DADA2 [15] and filtered as described [10]. We will calculate 95% confidence intervals of the mean change in abundance of each of the MDCF-2-responsive ASVs identified in this study, between day 0 and day 28, in children who received the reference MDCF-2 formulation, as well as the mean change in abundance for each of these ASVs in participants receiving the test formulations. A test formulation will be considered equivalent to the reference MDCF-2 if >70% of the MDCF-2-responsive ASVs have mean changes in abundance in children consuming a test formulation between day 0 and day 28 that fall within the 95% CI of their mean changes in abundance in the reference MDCF-2 arm. Another embodiment of the analysis of microbial community repair elicited by the reference MDCF-2 and test formulations will involve a comparison of their effects after 28 days of treatment on the abundances of metagenome-assembled genomes (MAGs) identified by shotgun sequencing of the same faecal DNA samples used to produce 16S rDNA amplicons.

Exploratory outcomes will include the effects of the test formulations on features of the plasma and faecal proteomes, including MDCF-2-responsive proteins that are associated with various facets of healthy growth using approaches described in the MDCF-2 POC study [10].

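### The 80% power behind 20 children per arm is a per-ASV screening figure from the earlier study, not the power of the trial's equivalence decision

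*Protocol article*

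**What the plan says.** The Sample size section of the protocol article starts from the POC study. The planning interval is defined thus: "We calculated 95% confidence intervals (CI; mean ± 1.96 standard error) for the change (delta) in abundance of each of the 209 ASVs", computed "for the 59 children in the MDCF-2 treatment group of the POC study". The resampling step uses "5000 subsets of 20 children from the MDCF-2 group and 5000 subsets of 20 children from the RUSF group". The result is reported as "we identified 121 ASVs whose mean changes in abundance for the MDCF-2 subsets fell within the 95% CI of the mean changes" of the 59 MDCF-2 participants, "but not in children who had received RUSF, with 80% power". The next sentence draws the sample size from it: "Therefore, each arm will include a minimum of 20 children who complete the study". Adding 15% for drop-out gives 23 recruited per arm.

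The Analysis plan section decides equivalence in another way. A test formulation passes if more than 70% of the responsive ASVs have test-arm mean changes "that fall within the 95% CI of their mean changes in abundance in the reference MDCF-2 arm". No power, assumed true difference or false-equivalence rate is given for that decision.

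**The concern.** Two things are wrong with using the 80% to justify 20 per arm.

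First, the MDCF-2 half of the screen compares children with themselves. Subsets drawn from the 59 have means centred on the midpoint of the interval by construction. The interval width and the spread of the subset means both scale with the same SD, so the SD largely cancels. What remains mostly reflects the ratio of 20 to 59.

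Second, the figure belongs to a different event. It concerns one ASV at a time and MDCF-2 against RUSF, with an interval from 59 children. The trial will compare a test formulation with kitchen-prepared MDCF-2, use an interval from its own reference arm, and count ASVs.

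The verdict is meant to select a shelf-stable product for larger studies. A reader would take 80% as the assurance behind that verdict, when the plan states neither the chance of passing an equivalent product nor the chance of passing one that behaves like RUSF.

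**Working it through.** **Inputs from the protocol article.** Sample size section: 59 children define the planning interval, multiplier 1.96, subsets of 20, 121 of 209 ASVs selected, 20 completers per arm. Analysis plan section: more than 70% of responsive ASVs inside the reference-arm CI. **Not given, so assumed below:** whether subsets were drawn with replacement, the distribution of the changes, the correlation between ASVs, and the true difference between foods.

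**1. Can the stated 80% be reproduced?** In SD units the planning half-width is 1.96/√59 = 0.255. For roughly normal changes:

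- Without replacement: SE = √((1 − 20/59)/20) = 0.182; 0.255/0.182 = 1.404; 2Φ(1.404) − 1 = 84.0%.
- With replacement: SE = 1/√20 = 0.224; 0.255/0.224 = 1.141; 2Φ(1.141) − 1 = 74.6%.

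The stated 80% lies between the two. It cannot be reproduced exactly without the ASV data, and it also includes a RUSF condition. Simulated heavy-tailed changes (t with 3 df) give similar averages, 84% and 76%. Sparse changes (10% of children non-zero) average 83% and 78% but vary more between ASVs: the 5th to 95th percentiles are 76% to 90% without replacement and 72% to 89% with.

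**2. Twenty independent children against the same 59-child interval.** SE of the difference = √(1/59 + 1/20) = 0.259; 0.255/0.259 = 0.986; 2Φ(0.986) − 1 = 67.6%.

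**3. The interval the trial will use.** With about 20 reference children the half-width is 1.96/√20 = 0.438 SD, which is √(59/20) = 1.72 times the planning half-width.

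**4. The trial's rule when the foods are identical.** With two independent arms of n, the half-width is 1.96/√n and the SE of the difference is √(2/n). The ratio is 1.96/√2 = 1.386 whatever n is, so the per-ASV chance is 2Φ(1.386) − 1 = 83.4%. With an estimated SD it is 80.1%, 81.7% and 83.0% at n = 10, 20 and 59. This quantity hardly depends on n, so it cannot yield 20.

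**5. The complete rule, by simulation.** Assumptions: 121 ASVs, so at least 85 inside (0.7 × 121 = 84.7); estimated SD; equal correlation of 0, 0.1, 0.3 or 0.5; every ASV shifted by the same amount in a random direction.

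| True shift | n | Probability of declaring equivalence |
|---|---|---|
| 0 | 20 | >99.9% / 98% / 90% / 83% |
| 0.2 SD | 20 | 84% / 82% / 78% / 73% |
| 0.3 SD | 20 | 12% to 29% over the four correlations |
| 0.3 SD | 10 | 65% to 68% over the four correlations |

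A smaller trial passes a food that differs by 0.3 SD more easily. This is the error that sample size controls under this rule.

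**6. A threshold case for RUSF.** Suppose an ASV on which POC RUSF subsets, drawn without replacement, fall outside the planning interval in 80% of draws. The difference must be 0.255 + 0.842 × 0.182 = 0.408 SD. In the trial, the chance of falling inside is Φ((0.438 − 0.408)/0.316) − Φ((−0.438 − 0.408)/0.316) = 0.534, so RUSF falls outside only 47% of the time. This is a per-ASV figure at the threshold; larger differences separate better.

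**The case against.** The 80% is attached to a joint condition, and the RUSF half uses different children. That half carries real information, so the whole figure cannot be called an artefact. This stands: the circularity concerns the MDCF-2 half only. It also stands that the hit rate is not the same for every ASV. The screen admits ASVs found in as few as 5% of samples, and sparse changes give variable rates. Whether draws were with replacement may be stated in a fuller document.

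Three stronger readings are tempting, and the documents do not support them.

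- **That 20 per arm is too few.** Identical foods pass in about 83% to more than 99.9% of simulations. The 47% in step 6 does not carry through to the verdict either. With all 121 ASVs at 0.41 SD, the chance of declaring equivalence is about 0.0001 if they are independent and below 1% when shifts go both ways. It reaches 0% to 32% only if all shifts share one direction, at correlations of 0 to 0.5.
- **That the 121 ASVs are largely chance selections.** If failing in RUSF means a hit rate below 80%, about 68% to 71% of ASVs would be selected with no food difference. If it means at most 20%, about 3% would be. The article does not define the term, so nothing follows about the 121.
- **That the same 121 ASVs carry the primary endpoint.** The Analysis plan refers to responsive ASVs identified in the present study, so using 121 in step 5 is an assumption.

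None of this supplies the missing link between the screening figure and the verdict.

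**Conclusion.** The concern holds in limited form. The 80% is a per-ASV screening figure from POC data, and deriving a minimum of 20 completers from it is a non sequitur. Its MDCF-2 half is set mainly by 20/59 for roughly normal changes (84% or 75%, depending on replacement) and exceeds the 68% expected of 20 independent children. The trial's decision differs in interval, contrast and counting rule. For identical foods its per-ASV chance is about 83% whatever the sample size, so the quantity that should inform sample size is the false-equivalence rate, and the plan gives none.

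The closed-form figures rest on near-normality. The figures for the complete rule also rest on assumed correlations, assumed shifts and a list of 121 ASVs. They show how the rule behaves and do not estimate this trial's power. What is shown to be wrong is the stated justification; the number 20 itself is not shown to be inadequate.

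**What to change.** 1. Withdraw the 80% power statement, or relabel it as the criterion by which ASVs were screened in the POC data, stating whether draws were with replacement and what failing in RUSF means.
2. Re-run the POC data with disjoint groups: 20 MDCF-2 children as reference, 20 other MDCF-2 children as test (40 of the 59), and 20 RUSF children. Apply the complete Analysis plan rule in each draw: reference-arm CI from 20 children, then the count of more than 70%. Using the actual children preserves the sparsity and the correlation between ASVs that had to be assumed above.
3. State two figures: the probability of declaring equivalence when the food is the same, and when the food is RUSF.
4. Keep 20 per arm. If the two figures do not support it, describe it as a precision or feasibility choice.

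The cost is a re-analysis of existing data and a restated paragraph, with no extra children and no change to trial procedures. Redefining responsive ASVs by a contrast with false-discovery control is a separate methodological choice and is not needed for this correction.

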### Intervention arms

The trial will have 5-arms designed to compare the efficacy of alternative MDCF formulations in repairing the gut microbiota of children with MAM compared to the repair produced by the current kitchen prepared MDCF-2 formulation. All the formulations are fortified with equal amount of vitamins and minerals. Children will be randomly assigned to one of the interventions after enrolment.Arm 1 - Reference control: kitchen-prepared MDCF-2Arm 2 - Individually packaged, pre-measured sachets of MDCF-2 ingredients, combined and reconstituted in the home setting prior to consumptionArm 3 - MDCF-2 shelf-stable foil pouch formulation with green banana powderArm 4 - MDCF shelf-stable foil pouch formulation with sweet potato instead of green bananaArm 5 - Ready-to-use supplementary food (RUSF)

Table 2 provides an overview of the interventions.

**Table 2 Tab2:** Arms and Interventions

	Arms	Intervention
1	Active Comparator: Central kitchen-prepared MDCF-2. Children randomized to this arm will receive 25g of kitchen-prepared version of MDCF-2 twice daily.	Dietary Supplement: Central kitchen-prepared version of MDCF-2. Kitchen-prepared MDCF-2 containing chickpea flour, peanut flour, soybean flour, green banana pulp, sugar, soybean oil and micronutrient mix. This version of MDCF-2 will be freshly prepared in a central kitchen on a daily basis and provided to participants on the same day.
2	Experimental: ‘Jump-start’ version of MDCF-2. Freshly reconstituted MDCF-2 ingredients. Children randomized to this arm will receive individually packaged MDCF-2 ingredients, combined into 21.7 g servings provided twice daily.	Dietary Supplement: Jump-start version of MDCF-2. Freshly reconstituted MDCF-2 ingredients. This version of MDCF-2 is comprised of its individually packaged ingredients. Separate premeasured sachets of chickpea flour, peanut paste, soybean flour, green banana powder, sugar, soybean oil and micronutrient mix will be combined and reconstituted prior to each feeding session.

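### The drop-out allowance is multiplied on instead of divided out: 23 recruited per arm gives 19.55 expected completers at 15% loss, just under the stated minimum of 20

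*Protocol article*

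**What the plan says.** The protocol article, Sample size, makes three linked statements. The number 20 comes from a resampling exercise on the earlier proof-of-concept data: "Using a bootstrapping approach with ASV data from 5000 subsets of 20 children from the MDCF-2 group", with the same number of subsets of the same size from the RUSF group. The exercise identified ASVs whose mean changes in the MDCF-2 subsets stayed inside the reference interval, "but not in children who had received RUSF, with 80% power". From this the article concludes: "Therefore, each arm will include a minimum of 20 children who complete the study". The recruitment figure follows: "Considering potential drop-outs (15%), 23 children will be recruited per arm".

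The Intervention arms section sets five arms, so the total recruited is 5 × 23 = 115. The article gives no inflation formula and does not say whether children who drop out are replaced.

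**The concern.** The three figures in the Sample size section (20 completers as a minimum, 15% drop-out, 23 recruited) cannot all hold as written. The 23 is what results from adding 15% of the completers to the completers. A drop-out rate is normally a share of those who start, so the required number is the completer target divided by the retained fraction. On that basis 23 is one child short in each arm, and the arm is expected to end just below a number that the article calls a minimum.

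What is at stake is the accuracy of a published sample-size statement. The 20 is the subset size to which the 80% figure is attached, so a reader will take 23 to be the recruitment that secures it at 15% loss. It does not quite do so.

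**Working it through.** **Inputs** (all from the protocol article)
- Completers required per arm: 20, stated as a minimum (Sample size).
- Drop-out: d = 15% (Sample size).
- Recruited per arm: 23 (Sample size).
- Arms: 5 (Intervention arms).

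**Step 1. Reproduce the plan's figure.** Multiplying by (1 + d): 20 × 1.15 = 23.0. This gives the stated number exactly.

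**Step 2. Standard inflation.** Dividing by (1 − d): 20 / 0.85 = 23.53, rounded up to 24 per arm, or 5 × 24 = 120 in total instead of 115.

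**Step 3. Back-check.**
- 23 × 0.85 = 19.55 expected completers, a shortfall of 20 − 19.55 = 0.45 of a child per arm.
- 24 × 0.85 = 20.4 expected completers.
- Largest loss at which 23 still leaves 20: 3 / 23 = 13.0%.

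**Step 4. Effect on precision.** At a fixed standard deviation the width of a confidence interval for a mean scales with 1/√n.
- 19.55 against 20 completers: √(20 / 19.55) = 1.011, about 1% wider.
- 19.55 against the 20.4 expected from recruiting 24: √(20.4 / 19.55) = 1.022, about 2% wider.

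**Step 5. Chance of meeting a hard minimum of 20.** This is illustrative. It takes the number of completers as binomial with retention 0.85, independent between children, with no replacement.

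| Recruited per arm | Expected completers | P(at least 20), one arm | P(at least 20), all five arms |
|---|---|---|---|
| 23 | 19.55 | 0.54 | 0.54⁵ ≈ 0.05 |
| 24 | 20.4 | 0.71 | 0.71⁵ ≈ 0.18 |

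The two rows must be read together. Correcting the arithmetic raises the one-arm chance from 0.54 to 0.71, but even with 24 all five arms reach 20 in fewer than one case in five. Most of the low all-arms figure comes from treating an expected number as a floor, and only part of it from the inflation slip.

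**The case against.** The best defence is that the point is too small to matter. In whole children, losing 3 of 23 leaves exactly 20. The gap between 13% and 15% is within the uncertainty of any planning guess about drop-out. One could also read the 15% as a share of the 20 completers, that is 3 children. The size argument stands: this is a correction of wording and arithmetic, not a design failure. The alternative reading does not rescue the sentence, because the allowance would then be 13% of those recruited, and the text would still need to say so.

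A second defence concerns what counts as a loss. The Analysis plan section needs samples at day 0 and day 28, whereas the Study design section adds two weeks of follow-up after treatment. A child lost in those last two weeks does not complete the study but can still enter the primary comparison. The article does not say when the 15% accrues. It is also a condensed account, so its silence on replacement does not show that there is none. This stands as a limit on the probabilities in the working. It does not alter the inflation arithmetic, because the stated requirement is for children who complete the study.

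Two stronger readings are tempting, and the documents support neither.
- A reader might infer that a short reference arm makes equivalence noticeably easier to declare, since the Analysis plan section judges test products against the reference arm's 95% confidence interval. The widening is about 1%, and a smaller test arm also has a noisier mean, which partly works the other way. Nothing in the article shows that this would change the result of the 70% rule.
- A reader might infer that all the planning calculations rest on 20 children and are therefore undermined. They do not: the planning confidence intervals come from 59 MDCF-2 children, and the 209 ASVs from 939 samples of 118 participants. Among the inputs, only the resampled subsets use 20.

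**Conclusion.** The stated recruitment figure is wrong for the stated assumptions, and nothing elsewhere in the article corrects it. The practical weight is low. The 80% figure belongs to subsets of 20, and an expected 19.55 is practically the same number.

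The arithmetic conclusion rests only on reading 15% as a share of the children recruited. The binomial probabilities rest on more: independent drop-out at exactly 15%, no replacement, and every drop-out counted as a non-completer. They should not be quoted as the cost of the slip. In particular, the 5% for all five arms with 23 should not be cited without the 18% for 24. Whichever recruitment number is kept, the word minimum promises more than the calculation can deliver.

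**What to change.** Restate the sentence in the Sample size section along these lines: *23 per arm gives 20 completers at up to 13% drop-out; about 19.5 are expected at 15%.* In the same place, describe 20 as an expected target and not as a minimum. This costs one sentence and leaves the design unchanged.

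For reference, keeping both the 15% allowance and an expected 20 completers requires 24 per arm, which is one more child per arm and five in total. The Current status of enrolment section says that recruitment was still under way when the article was written. If that route is taken, the text should say that 24 meets 20 in expectation only (20.4), so the change of wording from minimum to expected target is needed in either case.

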### Collection, preparation and archiving of biological samples

All biological samples (blood and faeces) will be collected according to the standard operating procedures (SOPs) described in our previous publications [11]. Five millimeters of blood will be collected from each participant before and after the treatment phase (Fig. 1). Whole blood samples will be centrifuged at 3000 x g for 10 minutes to separate the plasma [14]. Aliquots of plasma sample will be stored at -80 °C until analysis.

Faecal samples will be collected weekly during the run-in, treatment and wash-out phases of the study. At the site of collection, samples will be aliquoted into sterile, pre-labelled 2 mL cryovials and immediately placed into pre-charged liquid nitrogen dry cryo-shippers (within 20 minutes of their production by trial participants) for transport back to the laboratory. At the laboratory, vials will be placed on dry ice while they are organized and subsequently transferred to 9x9 freezer boxes. These boxes will be maintained in a -80^o^C freezer prior to analysis. No additives, preservatives or media will be added to the faecal samples.

### Analysis plan

To assess the comparability of microbiota repair elicited by shelf-stable test formulations of MDCF-2 and the reference kitchen prepared formulation, we will sequence PCR amplicons generated from variable region 4 of bacterial 16S rRNA genes present in DNA isolated from faecal samples collected from participants in the different study arms immediately prior to intervention (day 0) and at the end of intervention (day 28). ASV data will be processed using DADA2 [15] and filtered as described [10]. We will calculate 95% confidence intervals of the mean change in abundance of each of the MDCF-2-responsive ASVs identified in this study, between day 0 and day 28, in children who received the reference MDCF-2 formulation, as well as the mean change in abundance for each of these ASVs in participants receiving the test formulations. A test formulation will be considered equivalent to the reference MDCF-2 if >70% of the MDCF-2-responsive ASVs have mean changes in abundance in children consuming a test formulation between day 0 and day 28 that fall within the 95% CI of their mean changes in abundance in the reference MDCF-2 arm. Another embodiment of the analysis of microbial community repair elicited by the reference MDCF-2 and test formulations will involve a comparison of their effects after 28 days of treatment on the abundances of metagenome-assembled genomes (MAGs) identified by shotgun sequencing of the same faecal DNA samples used to produce 16S rDNA amplicons.

Exploratory outcomes will include the effects of the test formulations on features of the plasma and faecal proteomes, including MDCF-2-responsive proteins that are associated with various facets of healthy growth using approaches described in the MDCF-2 POC study [10].

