**Fig. 1 Fig1:**
[figure not shown]
Study design

It will be conducted in three phases. The first 2 weeks after enrolment are a ‘run-in’ phase where children are followed on their normal diets, without nutritional intervention. During this phase, collection of fecal samples will allow the baseline configuration of their microbiota to be characterized prior to treatment. Subsequently, participants will be randomized to receive one of the food prototypes, administered under supervision, twice daily for 4 weeks. Fecal samples collected at the end of the intervention phase will be used to assess the extent of microbiota repair produced by each treatment. After completion of the intervention, each child will be followed for another 2 weeks. Fecal samples collected during this phase will be used to assess the durability of the microbiota repair. Blood samples will be collected at baseline and at the end of the treatment phase to quantify levels of plasma protein biomarkers/effectors of healthy growth [11].

Eligible participants are 8-12-month-old Bangladeshi children with MAM. The study will be conducted among members of the slum population in Baoniabad of Mirpur, one of the 21 administrative units of the nation’s capital, Dhaka. Mirpur was selected because it is inhabited by poor and lower middle-class families, and because residential and sanitary conditions are typical of congested urban settlements. Additionally, the investigators have established several field sites in this area and have ongoing research activities in the community.

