### Outcome measures

Primary Outcome Measure: Equivalence in the response to MDCF-2 and a test MDCF formulation, based on the change in representation of MDCF-2 responsive gut bacterial taxa after 4-weeks of treatment. V4-16S rDNA amplicons and shotgun sequencing datasets will be generated from faecal samples collected from each child in each group prior to, during, and after treatment to determine the abundances of MDCF-2 responsive bacterial taxa. Equivalence will be defined as the absence of a statistically significant difference after 4-weeks of treatment in the representation of faecal bacterial taxa associated with the response to MDCF-2 in participants receiving a test MDCF, compared to the representation of these bacterial taxa in participants after receiving the reference MDCF-2 formulation for 4-weeks. Other pre-specified outcomes changes in the concentrations of faecal protein biomarkers of gut inflammation [myeloperoxidase (Alpco, Salem, New Hampshire), neopterin (GenWay Biotech, San Diego, California), calprotectin (BÜHLMANN fCAL, Schönenbuch, Switzerland), lipocalin-2 (R&D Systems, USA), dual oxidase 2 (MyBioSource, USA)] and protein losing enteropathy [alpha-1-antitrypsin (Biovendo Chandler, North Carolina)]. These proteins will be measured using commercially available ELISA according to the kit manuals. Changes in oxidation-reduction potential and pH of fecal samples will be quantified using a redox meter (PCE-228-R, PCE Instruments, Southampton, United Kingdom) and pH meter (Hanna Instrument, USA), respectively. In addition, changes in the abundances of 7000 circulating plasma proteins that include biomarkers and mediators of various facets of host physiology will be quantified using the SomaScan-aptamer-based proteomics platform (SomaLogic, Boulder CO, USA).

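### The primary equivalence rule uses an unadjusted change between one day-0 and one day-28 stool; a baseline-adjusted comparison would reduce false passes at little cost

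*Protocol article*

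**What the plan says.** The protocol article's Analysis plan sequences stools taken "immediately prior to intervention (day 0) and at the end of intervention (day 28" of the intervention. It then states: "We will calculate 95% confidence intervals of the mean change in abundance of each of the MDCF-2-responsive ASVs identified in this study", with the change running from day 0 to day 28 in the reference arm. A test formulation is equivalent if more than 70% of these ASVs have test-arm mean changes that "fall within the 95% CI of their mean changes in abundance in the reference MDCF-2 arm". No adjustment for the child's starting value is mentioned, and the abundance scale is not stated.

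More baseline material is available than this rule uses:

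- Study design: "The first 2 weeks after enrolment are a ‘run-in’ phase where children are followed on their normal diets, without nutritional intervention". In this phase, "collection of fecal samples will allow the baseline configuration of their microbiota to be characterized prior to treatment".
- Collection, preparation and archiving of biological samples: "Faecal samples will be collected weekly during the run-in, treatment and wash-out phases of the study".
- Outcome measures: sequencing data will come from "faecal samples collected from each child in each group prior to, during, and after treatment".
- Sample size: "each arm will include a minimum of 20 children who complete the study".

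**The concern.** An unadjusted change carries the full sample-to-sample noise of two single stools. It also carries any chance difference in baseline between arms of about 20 children. The run-in was built to measure baseline, yet the deciding comparison ignores every run-in sample except day 0 and uses day 0 only by subtraction.

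In this plan the acceptance window for each ASV is itself the reference arm's confidence interval, so noise widens the window. That matters for ASVs whose response to the test product really differs from the reference: a wider window lets more of them through. Wrongly accepting a non-equivalent product is the error that an equivalence study most needs to control.

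**Working it through.** **The plan's own figure.** From 20 completers and 15% drop-out, 20 × 1.15 = 23, which is the stated number per arm (20 / 0.85 = 23.5, rounded up to 24, is within one child). The 20 completers come from a bootstrap of proof-of-concept data that are not shown, so that step cannot be recomputed. I use n = 20 per arm below.

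**Inputs not in the article (assumptions).** The within-child correlation ρ, equal variance at each time point, and the number k of pre-treatment samples. A two-week run-in sampled weekly gives k = 3 if days −14, −7 and 0 are all sampled, otherwise k = 2. The exact days are not in the text, and Figure 1 is not shown.

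**Variance per child, in units of one sample's variance, at constant ρ.**

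- Unadjusted change: 2(1 − ρ).
- Adjusted for the mean of k pre-treatment samples: 1 − kρ² / (1 + (k − 1)ρ). With k = 1 (day 0 alone) this is 1 − ρ².

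| ρ | Change | Day 0 only | k = 2 | k = 3 |
|---|---|---|---|---|
| 0.3 | 1.40 | 0.91 (−35%) | 0.862 (−38.5%) | 0.831 (−40.6%) |
| 0.5 | 1.00 | 0.75 (−25%) | 0.667 (−33.3%) | 0.625 (−37.5%) |
| 0.7 | 0.60 | 0.51 (−15%) | 0.424 (−29.4%) | 0.388 (−35.4%) |

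For day-0 adjustment the direction is secure in large samples, because 2(1 − ρ) − (1 − ρ²) = (1 − ρ)², which is never negative.

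**Correlation that decays over time.** I took the correlation between samples t weeks apart as b + (1 − b − e)aᵗ, in seven settings. With k = 3 the reduction ran from 10.5% to 36.5%. The lowest value came from a pure weekly decay of 0.9 (b = e = 0). There, day 0 alone gave 17.2%, so averaging older samples lost part of the gain.

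**Chance imbalance.** With 20 per arm, the difference in baseline means between two arms has a standard deviation of √(2/20) = 0.316 sample SDs. Given such an imbalance, the difference in change is expected to shift by (1 − ρ) × 0.316, which is 0.16 at ρ = 0.5, where the SD of change is 1.00. Adjustment removes this shift.

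**Effect on the plan's rule, per ASV (normal approximation).** Let v be the variance relative to the unadjusted change and d the true difference in SDs of unadjusted change. The half-width of the window is 1.96·SE with SE = √(v/20), and the difference between the arm means has SD √2·SE.

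- d = 0: P(pass) = 2Φ(1.96/√2) − 1 = 0.834. The SE cancels, so v has no effect.
- d = 0.5, v = 1: SE = 0.2236, SD of difference = 0.3162. P = Φ((0.438 − 0.5)/0.3162) − Φ((−0.438 − 0.5)/0.3162) = 0.421.
- d = 0.5, v = 0.625 (ρ = 0.5, k = 3): SE = 0.1768, SD of difference = 0.25. P = 0.269.
- d = 0.5, v = 0.75 (ρ = 0.5, day 0 only): P = 0.33.
- d = 0.75: 0.162 unadjusted, 0.053 at v = 0.625.

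**The case against.** The strongest reply is that change from day 0 is a legitimate estimator in a randomised trial, and that describing baseline over a run-in does not oblige anyone to average it into the primary contrast. That stands: a reader might infer that the article contradicts itself, and it does not. It does not remove the point, because the article itself fixes the time points, the quantity, the interval and the pass rule. This is not a detail left open for a statistical analysis plan.

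Three stronger readings are tempting and are not supported.

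- That the variance cut is a known 35–40%. This needs three pre-treatment samples and a correlation that does not decay, and the article gives neither the correlation nor the sampling days. Much of the cut also comes from adjusting for day 0: moving on to the three-sample mean takes off a further 9% at ρ = 0.3 (0.91 to 0.83) and 17% at ρ = 0.5 (0.75 to 0.625).
- That wider intervals make equivalence easier to claim in general. For an ASV with no true difference, window and error scale together and the pass probability stays at 83.4%. Only ASVs that truly differ are affected.
- That adjustment is like enrolling many more children. It would not raise the pass rate of a truly equivalent product under this rule.

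It is also fair to say that constant correlation and equal variance are doubtful for a developing microbiota, and that ASVs detected in few samples may be mostly zeros. This limits confidence in the size of the gain. Finally, the Sample size bootstrap used the unadjusted change, so an adjusted analysis will not match it exactly.

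**Conclusion.** The point holds as a worthwhile improvement to the primary analysis, not as an error that invalidates it. The rule rests on an unadjusted change between two single stools while baseline information already being collected goes unused. At a constant within-child correlation of 0.3–0.7, variance would fall by about 15–35% with day-0 adjustment and about 29–41% with two or three pre-treatment samples. With decaying correlation the gain from the run-in mean could be about 10%. All these figures rest on an assumed correlation.

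What is gained is protection against chance baseline imbalance and fewer false passes: about 42% down to 27% per ASV at a true difference of 0.5 SD of change, for a 37.5% variance cut. These are per-ASV probabilities. How they carry over to the 70% threshold depends on how the ASVs vary together, which the article does not give.

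**What to change.** For each MDCF-2-responsive ASV, model the day-28 abundance, on the prespecified analysis scale, on arm and the child's baseline value. Estimate the adjusted mean of every arm at one common baseline, and use these means and the reference arm's adjusted 95% CI in the existing 70% comparison. Subtracting the common baseline from every arm changes nothing, so the result can still be reported as an adjusted change.

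Use at least day 0 as the baseline. Where the run-in samples are sequenced, use their mean including day 0, and fix that choice before the data are analysed. The day-0 version is the safer default if correlation is expected to fall quickly over time.

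The cost is some extra analysis and a note that the sample-size bootstrap was based on the unadjusted change. No new visits or enrolment are needed. Day-0 adjustment needs no further sequencing. If the earlier run-in stools are not already covered by the planned pre-treatment sequencing, adding one or two per child means 5 × 23 = 115, or 230, more samples.
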